### **2.2 Eligibility criteria**

#### **2.2.1 Inclusion criteria**

- 1.) At least 21 years of age
- 2.) Admitted to participating ICU/HDU
- 3.) Receiving nutrition at estimated goals for at least 24 hours
- 4.) ICU/HDU length of stay => 5 days

OR

Significant weakness as deemed by treating clinician below patient's baseline as a result of the ICU stay

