### **1.1 Statistical analysis and Sample size**

Trial will be prospectively registered on ANZCTR.

Efficacy of intervention will be analysed on an intention to treat basis. The analysis population is the intention to treat population defined as all study participants except for those who do not consent to use of data. There will be no imputation for missing data. A per protocol analysis will also be conducted including all participants with adherence to study medication of >80% of total study duration.

Normally and non-normally distributed data will be presented as mean and standard deviation (SD), and median and interquartile range (IQR), respectively. Between-group comparison of parametric data will be provided as mean difference and confidence interval and analysed using Student's t test. Between-group comparison of non-parametric data will be presented at median difference and analysed using the Mann-Whitney U test. For dichotomous data, frequencies and percentages will be presented and between-group analysis will use Fischer's Exact or Chi-squared test as appropriate. The numbers at risk in each group and the number and proportion of events observed will be reported, as well as the equivalent absolute risk difference, relative risk ratio and corresponding 95% confidence intervals. Survival time from randomisation until day 60, according to treatment group will be displayed as Kaplan-Meier curves and analysed using a log-rank test. Estimates of hazard ratios for survival, with corresponding 95% CI and P values, will be obtained from the Cox proportional hazards models incorporating treatment group alone, and independent covariates used in the multivariate models. Secondary analysis will also be conducted adjusting the primary outcome variable for prespecified baseline covariates (age, gender, APACHE-II score, BMI) in a transformed multivariable linear regression model including

baseline univariate variables with a  $p < 0.05$ . For all outcome analyses a two-sided P value of  $< 0.05$  will be considered significant.

Baseline variables recorded to demonstrate that the groups are comparable; if this is not demonstrated, *post-hoc* adjustments to correct for differences will be applied.

Sample size calculation: 60.

This is based on several different assumptions and outcome measures:

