1. Hospital length of stay, as sample of  $n=24$  per group has 80% power to detect a median difference of 3 days LOS (26 vs 23 days) with IQR 5.4 between independent groups (this is a conservative estimate as in the pilot, LOS results were 26 vs 36 days).
2. Time to walking with one-assist (ICU mobility scale). A sample of 24 per group has 80% power to detect a difference in proportions of 40 between the intervention and control groups, of patients walking with one assist at discharge (from a baseline of 27% in pilot).

To allow for loss to follow-up, the sample size number increased to 60.

Subgroup analysis: due to potential heterogeneity in patients, stratification based on MRC score,  $\geq 48$  (48 is an accepted cut off for ICU acquired weakness).

Economic evaluation:

An economic evaluation will be performed. Cost offsets from any reduction in LoS will be estimated separately for ICU stay and total hospital stay, and costed using hospital-specific per day costs. We will estimate QALYs using the SF-36 data converted to SF-6D using Australian population weights.(6)

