## **METHODS: ASSIGNMENT OF INTERVENTIONS**

### **Sequence generation**

A permuted block randomisation method will be used with variable block sizes, stratified by site.

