## **DATA COLLECTION, MANAGEMENT, AND ANALYSIS**

### **Data collection methods**

#### **Data Collection**

Data will be collected on a prespecified eCRF (RedCap - Research Electronic Data Capture - a secure web application for building and managing online surveys and databases) supported by a study-specific data dictionary and including checks of logical consistency and automatic query generation.

The following data will be collected:

- Age
- Gender
- ANZICS APD number

- Admission type (elective vs. emergency)
- ICU admission source (i.e. Emergency Department vs. ward vs. theatre vs. other hospital)
- Chronic APACHE co-morbidities
- APACHE-III admission diagnosis
- Illness severity based on the on the APACHE-II and III scores and risk of death, and “ANZ Risk of Death” models score
- ICU or HDA mortality
- ICU or HDA LOS
- Total duration of mechanical ventilation
- Total duration of vasoactive medication requirement
- Incidence and duration of renal replacement therapy
- Hospital mortality
- Post-ICU ward LOS
- Hospital disposition (home vs other acute care facility vs rehabilitation)
- ICU readmission
- Hospital readmission
- Day 60 mortality
- Inflammatory markers (CRP, Procalcitonin and WBC count at enrolment, ICU discharge and hospital discharge)
- BMI, weight at hospital admission, pre-admission medications.
- Baseline SF-36, FIM score and Barthel Index, to determine the patient’s pre-existing functional status (based on status two weeks prior to admission to ICU, from patient or surrogate).
- **Measurement of variables:**
  - **1. Laboratory tests**
    - Pregnancy test in women of child bearing age
    - Baseline: sex hormone binding globulin, testosterone.

- Routine blood tests will occur as planned by treating clinicians, and will collect:
- Haemoglobin, white cell count, albumin, urea and creatinine, alanine transferase.
- Lipids at baseline and at day 15-21.
- **2. Strength and weight measurements**
- a) Weekly: Hand grip strength, weight (kg) and MRC.
- **3. Other measures**
- Physiotherapy received - Duration of rehabilitation physiotherapy and mobility achieved (ventilation physiotherapy treatments will not be counted).
- Nutrition received - Caloric intake (kcal/total), Protein intake (g/total), Food intake (% of meals).
- **Follow-up**
- Phone call follow-up at 3 & 6 months using the SF-36 score , and asking about return to work (see script page).

*Pre-specified Subgroups:*

BMI at enrolment < 20

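### Baseline MRC score, the one factor the protocol names as a source of patient heterogeneity, is not a prespecified covariate, so its control rests on data-driven rules

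*Protocol*

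**What the plan says.** **Who enters.** Item 4 of section 2.2.1 has two routes joined by OR. One is "ICU/HDU length of stay => 5 days", with no weakness requirement. The other is "Significant weakness as deemed by treating clinician below patient's baseline as a result of the ICU stay", with no MRC threshold. Aims 1 to 3 in section 1.2 speak of deconditioned patients.

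**What is said about heterogeneity.** In section 1.1 (Statistical analysis and Sample size), under the label for subgroup analysis, the protocol writes "due to potential heterogeneity in patients, stratification based on MRC score". It puts the cut at 48, which it calls an accepted limit for ICU-acquired weakness.

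**How patients are allocated.** Sequence generation: "A permuted block randomisation method will be used with variable block sizes, stratified by site".

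**What is adjusted for.** The same section 1.1 gives the list as "prespecified baseline covariates (age, gender, APACHE-II score, BMI", and the adjusted analysis is secondary. It adds that the model includes baseline variables with univariate p < 0.05, and that post-hoc adjustments follow if the groups are not shown to be comparable.

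**Which subgroups are listed.** The pre-specified subgroups under Data Collection are "BMI at enrolment < 20" and admission cause. MRC is not there.

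**What is measured.** The first secondary outcome is change in MRC sum score from enrolment to discharge, extrapolated from available limbs where scoring is incomplete. MRC is also scored weekly.

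**The concern.** Strength at enrolment bears directly on when a patient walks with one assistant and when the patient goes home, which are the two primary outcomes. It is also the starting value of the MRC change score, a bounded scale on which stronger patients have less room to gain. The protocol recognises the mix of weak and stronger patients, but it then fixes a covariate list without the variable that describes that mix.

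Two things are at stake. The first is precision: a prognostic baseline value that is already being collected goes unused. The second is the reading of the one trial that is actually run. If one arm happens to hold more of the stronger patients, the unadjusted comparison is shifted, and whether an adjustment is made, and which one, is settled after the data are seen.

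**Working it through.** **Inputs.** From the protocol: 60 patients, 1:1 allocation, permuted blocks of variable size stratified by site, two-sided 0.05, MRC cut at 48, and four units that had expressed interest. Assumed, because the protocol does not give them: the share with MRC below 48 (30% to 70%), block sizes 2, 4 and 6, and the correlation r between enrolment MRC and a continuous outcome (0.3 to 0.6).

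**1. The plan's own figure.** For walking with one assistant, 27% against 67% at 80% power and two-sided 0.05 gives 24 per group, as stated. Then 48/(1 − 0.20) = 60, so the total fits a 20% allowance for loss. The length-of-stay leg gives 28 per group by the normal approximation (SD = 5.4/1.349 = 4.00), not 24. Nothing below depends on that leg.

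**2. Chance imbalance with exactly 30 per arm.** Let K of 60 patients have MRC below 48. The number X in one arm is hypergeometric, and the gap in share is (2X − K)/30.
- Var(X) = 30 × (K/60) × (1 − K/60) × 30/59.
- K = 30: Var = 3.81, SD of X = 1.95, SD of the gap = 2 × 1.95/30 = 13.0 points.
- K = 18 or 42: Var = 3.20, SD of X = 1.79, SD of the gap = 11.9 points.
- Probability of a gap of 20 points or more (6 patients): 0.196 for K = 30, 0.158 for K = 18 or 42.

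**3. The same with blocks within site.** Simulation with four sites and 20,000 runs:

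| Share below 48 | Strata | SD of gap | P(gap ≥ 15 points) | P(gap ≥ 20 points) |
|---|---|---|---|---|
| 30% | site | 0.118 | 0.207 | 0.102 |
| 50% | site | 0.130 | 0.247 | 0.137 |
| 70% | site | 0.119 | 0.210 | 0.104 |
| 30-70% | site and MRC | 0.046-0.051 | 0.001-0.003 | 0.000 |

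The SDs agree with step 2. The tail is lower because 20 points is exactly a possible value when each arm has 30 (steps of 2/30 = 6.7 points), but not when arm sizes vary. A fair range is 10-20%.

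**4. Would the data-driven rules catch it?** The protocol gives no criterion for comparability. Suppose it is p < 0.05 and the split is 18 v 12 of 30 (20 points). Chi-squared = 60 × (18² − 12²)²/30⁴ = 60 × 180²/810,000 = 2.4, p = 0.12. Fisher's exact p = 0.196. Nothing is triggered.

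The univariate rule can also be read as association with the outcome. With 60 patients that needs |r| above 2.00/√(2.00² + 58) = 0.25. By Fisher's z, the chance of entry is Φ(atanh(r)·√57 − 1.96): about 0.65 at r = 0.3 and 0.99 at r = 0.5. On that reading a strongly prognostic MRC would usually enter and a moderately prognostic one only sometimes. This presumes that MRC is a candidate at all, which the sentence leaves open.

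**5. What an imbalance of this size does.** If stays of weak and stronger patients differ by 3, 5 or 10 days (illustrative values), a 20-point gap shifts the unadjusted mean comparison by 0.2 × 3 = 0.6, 0.2 × 5 = 1.0 or 0.2 × 10 = 2.0 days. The target difference is 3 days.

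**6. Precision.** Linear adjustment multiplies residual variance by 1 − r²: 0.91 (r = 0.3), 0.75 (r = 0.5), 0.64 (r = 0.6). That is 9% to 36% less, and less again once the four listed covariates are in the model.

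**The case against.** Several points on the other side are sound.

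- **Imbalance would not simply go uncorrected.** A reader might infer that it would. Section 1.1 gives two routes, univariate p < 0.05 and post-hoc adjustment, and either could bring MRC in. What stands against them is that both depend on choices made after the data are seen.
- **The protocol does not contradict itself on randomisation.** A reader might take the MRC sentence as a promise of stratified allocation that Sequence generation breaks. The sentence sits under the label for subgroup analysis and most naturally means a stratified analysis. The wording is ambiguous, no more.
- **Chance imbalance does not inflate type I error.** The two-sided 0.05 level already covers it over repeated randomisations.
- **MRC is already a stated subgroup in section 1.1.** That is right, so its absence from the Data Collection list is mainly a cross-listing gap, though the two lists should agree.
- **Covariate choice is a judgement, and an analysis plan may add detail.** True in general. But this document fixes a list, and that list omits the one variable it names for heterogeneity.
- **Some patients cannot complete MRC scoring, and the protocol rules out imputation.** This is a real cost. It is limited because the protocol already extrapolates from available limbs.

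**Conclusion.** The point holds as a gap in prespecification. The protocol names MRC as the reason for heterogeneity, admits patients on both sides of the cut and measures the score at enrolment, but leaves it out of the fixed covariates and out of one of its two subgroup lists. Control of baseline strength is left to data-driven rules that can pass over a 20-point gap. Under the assumed 30-70% share below 48, a gap of that size or larger has roughly a 10-20% chance.

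The consequence is lost precision and conditional bias. The precision gain cannot be fixed from the documents: 9-36% less residual variance is what r = 0.3 to 0.6 would give for a continuous outcome with no other covariate. A reader might turn r = 0.5 into a saving of a third of the sample (1/0.75 = 1.33). The documents do not support that. They give no correlation, the protocol sizes time to walking as a proportion, length of stay is described by a median and IQR, and four other covariates are already listed.

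This is worth changing because the change is close to free. It does not threaten the validity of the randomised comparison.

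**What to change.** 1. In section 1.1, name enrolment MRC sum score, recorded before the first dose, as a fixed covariate in the adjusted analyses of both primary outcomes and of MRC change. Let this replace selection by univariate p < 0.05 and adjustment triggered by an observed imbalance.
2. Add MRC below 48 against 48 or above to the pre-specified subgroups under Data Collection, so that they agree with section 1.1.
3. State in section 1.1 that stratification by MRC means a subgroup analysis.

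The cost is wording, plus care that the score is taken before the first dose. The downside is that some baseline values will be extrapolated from available limbs, as the outcome definition already allows.

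Stratifying randomisation by MRC is optional and not needed. It would nearly remove the imbalance (step 3), but four sites by two MRC groups makes eight strata for 60 patients, an average of 60/8 = 7.5 each.

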## **METHODS: ASSIGNMENT OF INTERVENTIONS**

### **Sequence generation**

A permuted block randomisation method will be used with variable block sizes, stratified by site.

### **Allocation concealment**

Allocation concealment will be maintained by using sealed, sequentially numbered, opaque envelopes at each study site containing the study number corresponding to the allocated study number. Randomisation will not be performed until participants fulfil all eligibility criteria and are ready to be assigned to study treatment.

### **Implementation**

Participants will be enrolled in the study by ICU doctors, and research staff and study enrolment will be communicated to the bedside nurse who will implement the study intervention. Study drug will be prescribed on the medication chart as 'GAINS STUDY DRUG : NANDROLONE OR PLACEBO IMI'

### **Blinding**

Study medication will be provided blinded to treatment providers and trial participants through the use of a placebo. Syringes will be masked (sticker/alfoil) to prevent the contents being visualised to the administering nurse. Outcome assessment at 3 months, including SF-36, return to work will be conducted by a blinded research team member via telephone.

## **DATA COLLECTION, MANAGEMENT, AND ANALYSIS**

### **Data collection methods**

#### **Data Collection**

Data will be collected on a prespecified eCRF (RedCap - Research Electronic Data Capture - a secure web application for building and managing online surveys and databases) supported by a study-specific data dictionary and including checks of logical consistency and automatic query generation.

The following data will be collected:

- Age
- Gender
- ANZICS APD number

- Admission type (elective vs. emergency)
- ICU admission source (i.e. Emergency Department vs. ward vs. theatre vs. other hospital)
- Chronic APACHE co-morbidities
- APACHE-III admission diagnosis
- Illness severity based on the on the APACHE-II and III scores and risk of death, and “ANZ Risk of Death” models score
- ICU or HDA mortality
- ICU or HDA LOS
- Total duration of mechanical ventilation
- Total duration of vasoactive medication requirement
- Incidence and duration of renal replacement therapy
- Hospital mortality
- Post-ICU ward LOS
- Hospital disposition (home vs other acute care facility vs rehabilitation)
- ICU readmission
- Hospital readmission
- Day 60 mortality
- Inflammatory markers (CRP, Procalcitonin and WBC count at enrolment, ICU discharge and hospital discharge)
- BMI, weight at hospital admission, pre-admission medications.
- Baseline SF-36, FIM score and Barthel Index, to determine the patient’s pre-existing functional status (based on status two weeks prior to admission to ICU, from patient or surrogate).
- **Measurement of variables:**
  - **1. Laboratory tests**
    - Pregnancy test in women of child bearing age
    - Baseline: sex hormone binding globulin, testosterone.

- Routine blood tests will occur as planned by treating clinicians, and will collect:
- Haemoglobin, white cell count, albumin, urea and creatinine, alanine transferase.
- Lipids at baseline and at day 15-21.
- **2. Strength and weight measurements**
- a) Weekly: Hand grip strength, weight (kg) and MRC.
- **3. Other measures**
- Physiotherapy received - Duration of rehabilitation physiotherapy and mobility achieved (ventilation physiotherapy treatments will not be counted).
- Nutrition received - Caloric intake (kcal/total), Protein intake (g/total), Food intake (% of meals).
- **Follow-up**
- Phone call follow-up at 3 & 6 months using the SF-36 score , and asking about return to work (see script page).

*Pre-specified Subgroups:*

BMI at enrolment < 20

Admission cause :sepsis, neurological, post surgical.

Data will be collected by trained research co-ordinators at each site. Patients and/or their next of kin will be asked to provide three possible points of contact (home and close family contact details) to the research staff prior to discharge. Day 90& 180 (post hospital discharge) SF-36 will be conducted over the phone by a trained assessor.

For data collected by research co-ordinators at each site, data quality and protocol standardisation will be optimised by arranging a start-up meeting, providing an early on-site monitoring visit, regular feedback to each centre via phone and the trial web-site, and a monthly newsletter. A complete study procedures manual will be produced. All study personnel will have 24 hour access to the study coordinating centre to resolve any questions.

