## **2.3 Interventions**

### **2.3.1 Study interventions**

#### *Intervention*

Standard care (see below) with the addition of IMI nandrolone.

Dosing: Males: 100 mg weekly. Females: 50mg weekly – for 3 weeks or until hospital discharge, whichever is earlier.

The study drug will be drawn up by the ICU pharmacist, and then the syringe will be covered (to mask the contents of the syringe). All investigators, clinicians, nursing staff and patient are blinded.

NOTE: Dose change from the pilot study. The dosing was 200mg males/ 100mg females – however this is a large intramuscular volume, and can be difficult in patients without much muscle mass.

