### **Harms**

It is recognised that the intensive care patient population will experience a number of common aberrations in laboratory values, signs and symptoms due to the severity of the

underlying disease and the impact of standard therapies. Intensive care patients will frequently develop life-threatening organ failure(s) unrelated to study interventions and despite optimal management. Therefore, consistent with established practice in academic ICU trials, events that are part of the natural history of the primary disease process or expected complications of critical illness will not automatically be reported as serious adverse events in this study. All adverse events which are considered to be potentially causally related to the study intervention or are otherwise of concern in the investigator's judgement will be reported.

Potential side effects: Cardiac failure, Myocardial ischaemia, Virilisation in females (hoarseness, acne, hirsutism), abnormal LFTs, Polycythaemia, Increased sensitivity to oral anticoagulants.

Safety endpoints include: new onset hypertension (SBP>180units), abnormal liver function tests (ALT increase > 100% from baseline and >100), cardiac ischaemia or heart failure, virilisation in females.

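### Virilisation in females is a named safety endpoint, but the protocol schedules no assessment of it, either in hospital or at the follow-up calls

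*Protocol*

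**What the plan says.** The Harms section of the protocol lists "Virilisation in females (hoarseness, acne, hirsutism") among the potential side effects. The same section closes its list of safety endpoints with "cardiac ischaemia or heart failure, virilisation in females". It also contains a general reporting rule: "All adverse events which are considered to be potentially causally related to the study intervention", or which otherwise concern the investigator, are to be reported. That rule has no end date.

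Under 2.3.1 Study interventions, weekly injections are given "for 3 weeks or until hospital discharge, whichever is earlier".

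Contact after discharge is by telephone and is described in four places:

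- Data Collection, Follow-up: "Phone call follow-up at 3 & 6 months using the SF-36 score , and asking about return to work (see script page").
- Blinding: "Outcome assessment at 3 months, including SF-36, return to work will be conducted by a blinded research team member via telephone".
- Data Collection, on days 90 and 180 after discharge: "SF-36 will be conducted over the phone by a trained assessor".
- Primary and secondary outcomes: a phone call at 3 months using the SF-36.

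None of these mentions a safety question. The Data Collection list contains no virilisation item at any time point.

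**The concern.** A named endpoint needs a stated method and time of ascertainment. Here the protocol defines what counts (three signs) but not who looks for them, when, or until when. Injections can continue up to discharge, so some women may leave hospital shortly after a dose. The calls are then the only planned contacts described, and their described content does not cover the signs.

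If the signs are not asked about, a low count in the final report cannot be read as evidence that few women had them. A safety statement about women would then rest partly on who happened to mention a symptom. Analysis cannot repair this, because a statistical analysis plan can only use data that were collected.

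**Working it through.** The protocol gives no figure to reproduce. The check sets the endpoint against each place where it could be captured.

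1. **Definition.** Harms names the endpoint and gives three signs: hoarseness, acne and hirsutism. It gives no assessment schedule.
2. **In hospital.** The weekly measurements in Data Collection are grip strength, weight and MRC score. The laboratory items include alanine transferase, which serves the liver safety endpoint. Nothing on the list serves virilisation.
3. **After dosing.** By the dosing rule, all time after discharge is off study drug. A sign that appears or is noticed then can be recorded only through a later contact.
4. **Scheduled later contacts.** The four descriptions above name SF-36, return to work, or both. No post-discharge visit is described.
5. **Unscheduled route.** The general adverse event rule remains open after discharge. It requires that someone volunteers the symptom and that it is judged potentially related or of concern.

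So the visible plan has passive capture throughout and scheduled capture at no point.

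**Effect on the comparison.** Let p1 and p0 be the true proportions of women with virilisation signs in the nandrolone and placebo arms, and s the probability that a case is recorded. Assume s is the same in both arms and there are no false reports. The expected observed proportions are s × p1 and s × p0, and the observed difference is s × (p1 − p0). With s below 1, both proportions and their difference shrink towards zero. The protocol gives no basis for a value of s, so the shrinkage cannot be quantified.

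**What one case weighs.** The planned sample is 60, or 60 / 2 = 30 per arm. The protocol does not give the proportion of women. Assuming 30% to 50%:

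- 30 × 0.30 = 9 women per arm, and one case is 1 / 9 = 11 percentage points
- 30 × 0.50 = 15 women per arm, and one case is 1 / 15 = 7 percentage points

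This shows how sensitive the result is to a missed case. It does not estimate how many cases would be missed.

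**The case against.** The strongest reply is that the omission is not proven. The follow-up text points to a script page that is not in the text at hand, and the Blinding section introduces SF-36 and return to work with the word *including*, which is not exhaustive wording. The Data Collection list is also plainly incomplete: CPAx, a secondary outcome, is absent from it, as are blood pressure and cardiac events, which serve other safety endpoints. An eCRF with a data dictionary and a procedures manual are promised and could hold the item. Finally, the general adverse event rule has no cut-off at discharge, so a case volunteered at a call or seen at readmission is reportable.

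All of this stands against two stronger readings that a reader might infer: that the calls collect nothing but SF-36 and return to work, and that virilisation after discharge can never be captured. The document supports neither.

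A reader might also argue that a shorter stay on nandrolone gives that arm less inpatient observation and so biases the comparison towards safety. That is conditional on the treatment effect, and any figure for it would need an assumed enrolment day and the planning medians for stay. Likewise, the share of follow-up falling after discharge measures calendar time off drug, not lost events. The protocol says nothing about when signs would appear.

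The reply does not remove the main point. Passive reporting is a weaker means of capture than a scheduled question, and the timing and method of assessing a named endpoint belong in the protocol. If the script already asks, the sponsor need only say so.

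**Conclusion.** The point holds in a limited form. Virilisation in females is a pre-specified safety endpoint for which the protocol schedules no assessment, in hospital or afterwards. Unless the unseen script asks about it, cases noticed after dosing ends depend on unsolicited reports, and under-ascertainment in both arms is likely.

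This rests on one general assumption, that unprompted reporting finds fewer cases than direct questions. The extent of the loss cannot be calculated from the document. The number of women per arm used above (9 to 15) is an assumption.

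The primary analysis is not affected. The gap should be closed because it concerns safety, is inexpensive to repair, and cannot be made good once the calls have taken place.

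**What to change.** 1. Add a virilisation item for women to the inpatient eCRF, for example alongside the existing weekly measurements.
2. Add to the 3- and 6-month calls, for women in both arms, yes/no questions on hoarseness or voice change, acne, and new facial or body hair, each with onset and whether it persists. Ask them after both SF-36 and return to work are complete, so that the answers cannot influence those outcomes within the same call.
3. State in Harms that the endpoint is observed up to the 6-month call.
4. State that the 6-month caller is also blinded and does not see the 3-month virilisation answers. The Blinding section at present covers only the 3-month assessment, and Data Collection says only that the assessor is trained.

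If the script or eCRF already contains these items, a cross-reference in Data Collection and Harms is enough for items 1 and 2.

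**Cost.** One eCRF item, a few script lines and a minute or two per call, with no extra visit. Answers at the calls will rely on recall. There is a small risk that asking about androgenic signs at 3 months suggests the allocation to someone who later collects the 6-month SF-36; the question order and withholding the earlier answers limit that risk but do not abolish it. Dosing and clinical management are not touched.
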